## Abstract

Background: Immunotherapy has been successful in treating advanced melanoma, but a large proportion of patients do not respond to the treatment with immune checkpoint inhibitors (ICIs). Preclinical and small cohort studies suggest gastrointestinal microbiome composition and exosomal mRNA expression of PD-L1 and IFNγ from the primary tumor, stool and body fluids as potential biomarkers for response. Methods: Patients treated with immune checkpoint inhibitors as a first line treatment for metastatic melanoma are recruted to this prospective study. Stool samples are submitted before the start of treatment, at the 12th (+/−2) week and 28th (+/−2) week, and at the occurrence of event (suspected disease progression/hyperprogression, immune-related adverse event (irAE), deterioration). Peripheral venous blood samples are taken additionally at the same time points for cytologic and molecular tests. Histological material from the tumor tissue is obtained before the start of immunotherapy treatment. Primary objectives are to determine whether the human gastrointestinal microbiome (bacterial and viral) and the exosomal mRNA expression of PD-L1 and IFNγ and its dynamics predicts the response to treatment with PD-1 and CTLA-4 inhibitors and its association with the occurrence of irAE. The response is evaluated radiologically with imaging methods in accordance with the irRECIST criteria. Conclusions: This is the first study to combine and investigate multiple potential predictive and prognostic biomarkers and their dynamics in first line ICI in metastatic melanoma patients.

## 1. Introduction

Melanoma is a dangerous form of skin cancer, accounting for around 5% of all skin cancers and responsible for more than 90% of skin cancer deaths [1,2,3]. Although the survival rate is improving, the prognosis depends on the stage at diagnosis [4,5,6,7]. In the last decade, immunotherapy has achieved the greatest advance in the treatment of disseminated melanoma. The median overall survival rate was greatly extended, thus giving hope to many patients. However, only up to 50% of patients respond to immunotherapy treatment. Severe immune-related adverse events (irAE) may occur during treatment, and some patients have no or minimal benefit from immunotherapy treatment due to primary or acquired resistance [8]. There is a need to implement biological markers in clinical practice to improve personalized treatment and to predict response to treatment [7]. The absence of clinically validated predictive biomarkers is one of the biggest causes of the unpredictable effect of immunotherapy [9]. Based on the existing literature, the microbiome, PD-1/PD-L1 (programmed death-ligand 1/ programmed death 1) signal pathway and Interferon-gamma (IFN-γ) are suggested as possible biomarkers, but further studies are needed to obtain relevant clinical information on larger cohorts.

### 1.1. Immunotherapy with Immune Checkpoint Inhibitors in the Treatment of Malignant Melanoma

The immune system plays an important role in carcinogenesis. The suppression of immune system creates a favorable tumor microenvironment that promotes the growth and development of cancer cells. In recent years, a breakthrough in oncology has been achieved by immunotherapy with immune checkpoint inhibitors (ICIs). ICIs are monoclonal antibodies that, by binding to PD-L1/PD-1 and CTLA-4 (cytotoxic T-lymphocyte-associated protein 4), enable immune cells to act against tumors [10]. *PD-1* is a transmembrane receptor on various cells of the immune system (T and B lymphocytes, macrophages, natural killer cells and dendritic cells). Transmembrane glycoprotein *PD-L1* is found on immune cells, such as macrophages, some activated T and B lymphocytes, dendritic and epithelial cells, and is also present on tumor cells, where it enables so-called “immune escape”. The binding of PD-1 to PD-L1 initiates a negative regulatory loop of T lymphocytes and other immune cells, thereby enabling the proliferation of cancer cells. According to recent research, PD-L1 can also independently activate proliferative tumor pathways (PI3K/AKT, MAPK, JAK/STAT, Hedgehog and others) [11]. CTLA-4 appears as a protein receptor in regulatory T lymphocytes and, by binding to the B7 protein on antigen-presenting cells, initiates the inhibition of the immune response [5].

Immunotherapy with PD-1/PD-L1 and CTLA-4 inhibitors in the treatment of patients with metastatic malignant melanoma has greatly improved prognosis and survival. Life expectancy has increased from less than 12 months to more than 40 months. Immunotherapeutics from the group of PD-1 inhibitors (nivolumab, pembrolizumab), a combination of two-tier immunotherapy of PD-1 and CTLA-4 inhibitors (nivolumab and ipilimumab) and BRAF inhibitors (vemurafenib, dabrafenib)—and MEK (cobimetinib, trametinib) signaling pathways in the case of BRAF V600 mutation—are used as the first line treatment for metastatic melanoma according to ASCO and NCCN guidelines [12].

Unlike BRAF and MEK inhibitors, which inhibit signaling through the RAS–RAF–MEK signaling pathway, the action of immunotherapy is much more complex and therefore more unpredictable. In approximately 10% of patients, the response to immunotherapy treatment manifests as pseudoprogression, with a discrepancy between the clinical and radiological response and the actual response due to a transiently violent inflammatory response. Up to 30% of patients respond to immunotherapy treatment with hyperprogression, where, for as yet unknown reasons, the cancer progresses rapidly. More than a third of patients have irAE when treated with ICI, but regardless, treatment interruption or discontinuation has a better response and longer progression free survival [13,14,15].

### 1.2. Human Gastrointestinal Microbiome, PD-1/PD-L1 Signal Pathway and Interferon-Gamma (IFN-γ) as Prognostic and Predictive Biomarkers

#### 1.2.1. Human Microbiome

The human microbiome is a genetic set of all microbes in the human organism including bacteria, viruses, fungi and protozoa. It consists of approximately 100 trillion microorganisms that encode more than three million genes and thousands of metabolites [16]. The microbiome affects metabolic homeostasis, metabolism and neurological development, and also plays an important role in the immune response [17,18]. An imbalance between the microbiome and its host is believed to have an impact on the occurrence of many diseases, such as cancer and autoimmune, metabolic and infectious diseases. The composition of the microbiome is influenced by environmental factors during and after birth, childhood and adulthood, and it also changes with diet and nutrition [19].

Recently, techniques for more precise analysis of the microbial genome and the interactions between the microbiome and its host have been rapidly developed. DNA sequencing technology, together with advances in bioinformatics, enables the amplification and sequencing of target microbiological DNA regions, followed by statistical analysis and grouping of microorganisms according to the collected databases. When studying the bacterial genome, we use the target of the 16S ribosomal gene (16S rDNA), a hypervariable sequence, on the basis of which we distinguish individual bacterial genera. Metagenomic sequencing is also in use, which allows a more precise insight into the so-called microbial metagenome (set of all microbial genes from an ecosystem) and simultaneous identification of the composition of the microbiome down to the level of bacterial species, as well as insight into the composition of the so-called virome, i.e., part of the microbiome that includes bacteriophages and eukaryotic viruses [16].

#### 1.2.2. Immunobiology and the Human Gastrointestinal Microbiome

The largest concentration of microbes and lymphoid tissue is in the gastrointestinal tract (GIT), where the immune system and the microbiome are in symbiosis [18]. The microbiome participates in the production of cytokines, regulates the T cell response and maintains homeostasis [19]. It has been demonstrated that changes in the composition and density of the GIT microbiota locally affect the immune response, but the question of the effect on the immune and inflammatory response at the systemic level arises [20]. The influence of the microbiome on systemic immunity is mainly attributed to the activation of specific regulatory T cells and the production of interleukins (interleukin 9 and others) [21].

#### 1.2.3. Immunotherapy with Immune Checkpoint Inhibitors and the Microbiome

Despite the great success of the treatment of metastatic malignant melanoma with immunotherapy, some patients do not respond to the treatment, or develop severe adverse side effects during the treatment that prompt discontinuation of the treatment. Some biomarkers of the tumor microenvironment that predict the response to immunotherapy treatment are already known, such as tumor mutational burden (TMB) and microsatellite stability (MSS). Some of the studies carried out so far suggest the GIT microbiome and its cytokines as potential biomarkers of carcinogenesis, and that they could also serve as predictive biomarkers of response to treatment with PD-1 and CTLA-4 inhibitors. The impact of dysbiosis due to antibiotic use on the efficacy of treatment with PD-1 and CTLA-4 inhibitors has been reported, as has the improvement of responses to treatment with immune checkpoint inhibitors in patients after fecal microbiome transplantation (FMT) [8].

#### 1.2.4. PD-1/PD-L1 Signal Pathway

The PD-1/PD-L1 signaling pathway is an important mechanism for immune escape and tumor progression. Recent research has shown that patients with overexpression of PD-L1 in their tumor tissue benefit more from treatment with programmed cell death protein 1 (PD-1) and PD-L1 inhibitors [22,23]. Programmed cell death receptor 1 (PD-L1) on the surface of tumor cells inhibits the antitumor activity of T lymphocytes by binding to their PD-1 receptor and causes immunosuppression [24,25]. PD-L1 is a promising predictive biomarker for predicting response to immunotherapy treatment. An alternative to membrane-bound PD-L1 is exosomal PD-L1 (ExoPD-L1), secreted from tumor cells, whose expression correlates with membrane-bound PD-L1 on the surface of the parental tumor cell [24,25]. The predictive role of PD-L1 is controversial, as around 10% of patients who do not express PD-L1 in tumor tissue also respond to immunotherapy. This is probably related to the immune microenvironment of the tumor, where PD-L1 is also expressed on immune cells (on helper T cells—CD4+, killer T cells—CD8+, regulatory T lymphocytes—Treg, B lymphocytes, killer cells—CD56+ and monocytes -macrophage cells) and contributes to antitumor immunity.

PD-L1 expression is dynamic and variable with patient and tumor heterogeneity and may depend on several factors, including prior therapies and the presence of tumor-infiltrating immune cells [12]. The expression can vary from the tumor margin to the core, between the primary tumor and metastases, and change dynamically during disease progression. Consequently, a biopsy from tumor tissue at a given time is not representative enough to determine the PD-L1 status of a tumor. Given the lack of detection of PD-L1 by conventional biopsy and IHC, research is focusing on the expression of circulating PD-L1 in serum, plasma, circulating tumor cells, and exosomes, which are minimally invasive and obtain real-time detection for a more accurate representation of heterogeneous PD-L1 expression [23,26].

The gut microbiome and its interactions with the tumor microenvironment, up- and down-regulating a beneficial immune response, could be a potential predictive biomarker for immunotherapy efficiency. The data has shown that beneficial gut microbiota in responders enhance the activation and expression of CD cells and promote CD cell activation, as opposed to non-responders with unfavorable gut microbiota and a higher frequency of Tregs [27].

#### 1.2.5. Interferon Gamma

Interferon Gamma (IFNγ) is a cytokine with antitumor and immunomodulatory activity [28].

It is formed by the cells of the immune system—cytotoxic T lymphocytes (CD8+TLy), helper T cells (CD4+TLy) and natural killer cells (NK cells) [29]. IFNγ acts by activating the JAK/STAT signaling pathway, which modulates the transcription of several genes [30]. Some of the end products of these genes inhibit the growth of tumor cells, while others contribute to it. The anti-tumor activity of IFNγ is manifested by the activation of antigen-presenting cells, the arrest of the cell cycle in the G1 phase, the stimulation of cell ischemia and apoptosis. Pro-tumor activity is caused by T cell suppression and inhibition of NK cell activity, stimulation of programmed cell death ligand 1 (PDL1) expression on tumor cells and stimulation of angiogenesis and tumorigenesis [28].

Recent research has shown that IFNγ reflects the state of response to immunotherapy. Higher concentrations of IFNγ before starting the treatment are associated with a better response to treatment [30,31,32]. Reduced expression of genes encoding the synthesis of IFNγ itself or its receptor, as well as genes that are part of the JAK/STAT pathway, results in its reduced activity and, consequently, resistance to treatment with immune checkpoint inhibitors [33,34,35,36,37]. Some recent studies have also shown that the gut microbiome modulates IFNγ response and plays a role in opportunistic infections and autoimmune diseases [38,39].

#### 1.2.6. Rationale for the Study

The specific composition and biodiversity of the gastrointestinal microbiome, exosomal mRNA expression of PD-L1 and IFNγ and dynamics predict the response to immunotherapy treatment with immune check point inhibitors and could serve as prognostic and predictive markers.

The studies published so far have been carried out on animal models or a small number of subjects or samples. We attribute the conflicting results of the studies conducted so far to this. The importance of intestinal flora in health or pathology and the influence and connection of inflammation and immune cells is a developing medical topic. It is for this reason that many studies are based on small cohorts and a small number of samples, especially in the field of oncology. Our study is pioneering precisely in this respect, as it is composed thoroughly, with a clear hypothesis, on a large cohort and number of samples. Samples will be taken at three different treatment points and at any event such as hyperprogression, pseudoprogression or immune-related side events. We will study the dynamics of changes in the diversity of the GIT microbiome and the systemic immunological response during the treatment of metastatic melanoma with immunotherapy.

The study is first prospective study that simultaneously determines the expression of IFNγ and PD-L1 in tumor tissue and blood at different time points. If we demonstrate that there is a correlation in the expression of IFNγ and PD-L1 in the tumor tissue and the blood, IFNγ could be obtained from the patient’s peripheral blood by a minimally invasive method.

## 2. Methods and Design

### 2.1. Study Design

The study is cohort-prospective, non-randomized and non-interventional (Figure 1). It will assess the association between the predominant composition of the human gut microbiome and the response to immunotherapy treatment with PD-1 and CTLA-4 inhibitors in metastatic malignant melanoma. It will also observe whether specific biomarkers (host immune cells population, PD-L1 and IFNγ expression) correlate with the predominant composition of the gut microbiome and the response to treatment with immunotherapy.

Patients with metastatic malignant melanoma who will be treated with immunotherapy in the first line in the three-year period from October 2022 to October 2025 will be included in the research. One-hundred-and-fifty patients will be included. Consenting patients will be asked to provide clinical data and donate biological samples before, during and after completing their treatment. Patient data will be anonymized—date of birth, gender, date of diagnosis, performance status at initiation of treatment, liver enzymes, tumor markers—LDH, S100, localization, BRAF status, treatment type, response to immunotherapy, treatment time, immune-related adverse events of treatment.

### 2.2. Study Objectives

#### 2.2.1. Primary Objectives

To determine the relationship between the predominant composition of the human gastrointestinal microbiome and the objective response to treatment with ICIs in patients with metastatic malignant melanoma.To determine whether the dynamics of exosomal mRNA expression for PD-L1 and PD-L1 on the surface of immune cells is related to the response to immunotherapy treatment and has predictive value.To determine whether the exosomal mRNA expression for IFNγ is related to the response to immunotherapy treatment and has a predictive value.

#### 2.2.2. Secondary Objectives

To determine whether a specific composition of the microbiome is associated with the occurrence of immune-related side effects in treatment with ICIS.To determine the effects of ICI on the gut microbiota over different time points.

#### 2.2.3. Exploratory Objectives

To determine if there is a relationship between a certain composition of the microbiome and the cell population (CD3+, CD4+, CD8+, the ratio between CD4+ and CD8+, macrophages) in the peripheral blood.Whether patients who develop immune-related side effects when treated with immunotherapy have a better response to it and longer survival without disease progression compared to patients who do not develop immune-related side effects.

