#### 2.3.6. Assessments during the Study

Patients will be followed up at their routine visits at the clinic. The follow-up will be scheduled at 3- or 4-week intervals, depending on the ICIs treatment regimen, when routine examination and laboratory test will be taken. Study-specific data will be collected at three different time points: up to 4 weeks before the start of treatment, at the 12th (+/−2 weeks) and 28th week (+/−2 weeks). Study-specific data will be taken additionally, if suspected disease progression and the appearance of immune-related adverse events or if indicated by the oncologist (Table 1).

Patients will be followed up regularly for the time of the treatment for the first 12 months. The study will be prematurely terminated in an event occurrence defined as disease progression/hyperprogression; by the physician’s choice in severe immune-related adverse events; when high doses of systemic corticosteroid (dexamethasone 4 mg/day or equivalent or higher) or prolonged antibiotic treatment are present; or by the patient’s choice. Before each stool sample donation, the patient will fulfill a questionnaire regarding eating habits, alcohol and tobacco consumption and medications. In the case of antibiotic treatment, the stool sample will be donated after 3 weeks of the last antibiotic dose taken.

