
#### 2.5.3. Imaging Assessments

Patients will undergo diagnostic imaging (CT of the head, chest and abdomen or PET-CT) up to 4 weeks before the start of treatment, the 12th (+/−2) and 28th (+/−2) weeks after the start of treatment and at the occurrence of the event (in case of suspicion of disease progression, the occurrence of immune-related side effects, deterioration of the condition, etc.).

The response to the treatment will be evaluated radiologically with imaging methods in accordance with the irRECIST criteria (criteria for evaluating the immune response in solid tumors). The irRECIST criteria divide the response to treatment into individual groups: complete response (CR, complete response); partial response (PR, partial response); stagnation (SD, stable disease); and progression (PD, progressive disease). Pseudoprogression is defined as a transient radiological progression of the disease without a clinical picture and a gradual reduction of the burden of the underlying disease.

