#### 2.5.4. Statistical Methods

The gastrointestinal microbiome, PD-L1 and Interferon Gamma expression will be correlated with one year of PFS as the primary outcome of the study. An interim analysis will be made after the first 20 included patients.

We will analyze the 16S rRNA sequences with the appropriate software tools from the Mothur software package, and we will perform analysis of molecular variance (AMOVA) and principal coordinate analysis (PCoA). For the statistical analysis of the differences in the representation of the sequences of individual bacterial groups in the studied microbiomes, we will use the DeSeq 2 package from the R programming environment. The association between phylogenetic diversity, taxonomic units, immune cells and the objective response to treatment will be determined using the Wilcoxon test. To compare values at different time points, we will use the paired *t*-test or corresponding non-parametric alternative. When comparing several groups at the same time, we will use the Kruskal–Wallis test. All differences will be considered statistically significant when *p* < 0.05.

The Kaplan–Meier method will be used to calculate survival (PFS), and the survival comparison of multiple groups will be calculated using the log-rank test. The association between the change in PD-L1 or IFNγ expression and response to treatment will be assessed using a logistic regression model and a multivariate model in which different variables will be included. Pearson’s or Spearman’s correlation test will be used to correlate changes in PD-L1 or IFNγ expression levels in tumor and blood.

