## Figures and Tables

**Figure 1 biomedicines-11-02016-f001:**
[figure not shown]
Study flow chart.

**Table 1 biomedicines-11-02016-t001:** List of assessment activities.

	Baseline (4 Weeks or Less before First ICI Application)	Before Every Cycle	12. and 28. Week (+/−2 Weeks)	Progression Disease	Immune-Related Adverse Events
Written consent	X				
BRAF/NRAS status	X				
Clinical examination	X	X		X	X
Personal history	X				X
Laboratory tests	X	X	X	X	X
LDH and S-100	X	X	X	X	
Thyroid function	X	X			X
Immune-related adverse side effects		X	X	X	X
Blood sample	X		X	X	
Stool sample with questionnary	X		X	X	X
CT head, thoracic and abdominal cavity/PET CT + CT head	X		X	X	

**Table 2 biomedicines-11-02016-t002:** Primer details for IFNgama sequence and CD274 (PD-L1) sequence.

Primer	Primer Details	Reference Sequence Number	Assay ID
IFNgama	Expression primer specific for the human IFNgama sequence	NM_000619	Hs.PT.58.3781960
CD274	Expression primer specific for the human CD274 sequence	NR_052005	Hs.PT.58.20819087

**Table 3 biomedicines-11-02016-t003:** Detail description of the used antibodies for flow-cytometric analysis.

Marker	Flurochrome	Clone	Manufacturer	Cat. Number	Volume Used Per 100 µL of Blood Sample/Tube
CD45	V500	HI30	BD	560777	2 µL
CD14	APC-Cy7	MφP9	BD	561709	2 µL
CD68	PE	Y1/82A	Biolegend	BZ-333808	5 µL
CD11b	FITC	Bear-1	Beckman Coulter	IM0530U	10 µL
CD206	PerCP-Cy-5.5	15-2	Biolegend	BZ-321122	5 µL
PD1 (CD279)	PE-Cy7	EH12.1	BD	561272	5 µL
PDL1 (CD274)	APC	MIH1	BD	563741	5 µL
CD4	FITC	SK3	BD	345768	3 µL
CD3	PerCP-Cy5.5	SK7	BD	332771	3 µL
CD8	APC-Cy-7	SK1	BD	348813	3 µL
CD103	PE	Ber-ACT8	Biolegend	350206	5 µL

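### Section 2.5.3 makes an irAE a reason for imaging and Table 1 does not; if section 2.5.3 holds, the exploratory irAE comparison rests on unequal imaging after week 28, with a modest effect

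*Protocol article*

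**What the plan says.** **The comparison.** Section 2.2.3 asks whether "patients who develop immune-related side effects when treated with immunotherapy have a better response to it and longer survival without disease progression", set against patients who have none. It is an exploratory objective.

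**Scheduled imaging.** Section 2.5.3 sets scans at baseline and at "the 12th (+/−2) and 28th (+/−2) weeks after the start of treatment". No later study scan is scheduled.

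**Prompted imaging.** The same section adds a scan "at the occurrence of the event (in case of suspicion of disease progression, the occurrence of immune-related side effects, deterioration of the condition, etc". The irAE stands there as a trigger of its own, with no grade threshold.

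**Table 1.** The row "CT head, thoracic and abdominal cavity/PET CT + CT head" is marked at baseline, at weeks 12 and 28, and at progression. Its irAE cell is empty.

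**Horizon and method.** Section 2.5.4 says the biomarkers "will be correlated with one year of PFS as the primary outcome of the study". It gives no separate horizon for the irAE comparison. Section 2.3.6 states: "Patients will be followed up regularly for the time of the treatment for the first 12 months". For survival, section 2.5.4 names Kaplan–Meier and says "the survival comparison of multiple groups will be calculated using the log-rank test". It says nothing about progression first seen on an unscheduled scan.

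**The concern.** Under section 2.5.3, belonging to the irAE group changes how hard progression is looked for. A patient with an irAE can have a scan with no suspicion of progression. A patient without one is scanned at weeks 12 and 28, or when something is suspected.

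Up to week 28 the scheduled scans let the irAE-free patients catch up. After that there is no common scan, so a progression without symptoms or signs may surface in one group and stay unseen in the other until the one-year cut-off. The analysis uses detection dates, so a difference in looking can appear as a difference in PFS.

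Response may also be affected. If it is taken as the best result on any scan, an extra scan is an extra chance to record a complete or partial response. The article does not say that best response is the measure, so this part is conditional and I put no size on it.

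**Working it through.** **1. Is there an extra scan?** The document gives two answers.

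| Place | Imaging at irAE |
|---|---|
| Section 2.5.3 | Yes, listed as a trigger |
| Table 1, CT/PET-CT row | Not marked |
| Table 1, blood row (for comparison) | Not marked, although section 2.4.1 takes blood at an irAE |
| Section 2.3.7 | Imaging results are among the irAE data collected |

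The blood row shows that a blank in Table 1 is not reliable proof of absence. Neither reading can be taken as settled.

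**2. Size if section 2.5.3 holds.** The article gives no PFS rate, event count or effect size, so there is no figure to reproduce. The size comes from simulation with progression and irAE independent of each other.

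Assumptions, not in the documents: exponential times; one-year PFS 35–55%; an irAE within the year in 35–50%; an exponential delay from progression to clinical suspicion (the silent phase) averaging 1, 3 or 6 months. Scans fall at weeks 12 and 28 (±2), with one more half a week after the irAE. The irAE is time-dependent, and the measure is a Mantel–Haenszel rate ratio in weekly bins, irAE versus none.

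| Mean silent phase | Whole year | Weeks 30–52 only |
|---|---|---|
| 1 month | 1.02 | 1.01–1.03 |
| 3 months | 1.08 | 1.15 |
| 6 months | 1.13 | about 1.4 |

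Without irAE-prompted scans the ratio is 0.99–1.01.

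**3. Hand check of the late window.** Take a progression arising evenly over weeks 30–52 (22 weeks) and a mean silent phase of 13 weeks. Let u be the time left to week 52.

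- No irAE scan: the share undetected is (1/22)∫e^(−u/13)du = 13(1 − e^(−22/13))/22 = 10.61/22 = 0.48, so 52% are detected.
- An irAE at a random time in the window: the integrand is multiplied by (1 − u/22), giving (10.61 − 85.23/22)/22 = (10.61 − 3.87)/22 = 0.31, so 69% are detected.

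The simulation, with exponential progression, gives 54% and 71%.

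**4. A different model.** Here 30%, 50% or 70% of progressions are found only by a scan, median progression is 26, 52 or 78 weeks, 36% have an irAE (uniform over weeks 2–52), and irAE is a fixed label. The rate ratio is 1.04–1.10. Observed one-year PFS is about 1 to 4 points lower with irAE: 56.9% versus 59.3% at median 52 weeks and 50% silent, and 36.4% versus 40.5% at median 26 weeks and 70% silent. On the Table 1 reading the ratio is 1.00–1.01.

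**5. Direction under other handling of irAE timing**, still with no true effect.

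- Simple yes/no grouping by an irAE seen before progression: the second model gives 0.39–0.44 with irAE scans and 0.33–0.38 without. Immortal time dominates, because irAE patients must stay progression-free until their irAE.
- Landmark at week 30: about 0.86–0.99. After the landmark, first irAEs and their scans occur only in patients labelled irAE-free, so the effect reverses.

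**6. Against the noise.** Power = Φ(√(d·p(1−p))·|ln HR| − 1.96). At HR 1.15 with an assumed d = 60 events and p = 0.34: √13.46 × 0.140 − 1.96 = −1.45, so 7%. With d = 90 and p = 0.40: √21.6 × 0.140 − 1.96 = −1.31, so 10%. A distortion of this size would seldom produce a significant result alone.

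**The case against.** The strongest reply is that Table 1 prescribes no imaging at an irAE, and without it the effect vanishes. That stands as far as it goes, and it is why the contradiction is the first thing to settle. It does not dispose of the point, because section 2.5.3 is explicit and Table 1 has at least one other doubtful blank.

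Second, the silent phase is assumed. Section 2.3.6 has visits every 3 or 4 weeks, and Table 1 has examination, LDH and S-100 before every cycle in all patients. A 6-month average may therefore be too long. This stands: the upper figures are an outer range.

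Third, some irAE patients leave early. Section 2.3.6 allows termination at the physician's choice "in severe immune-related adverse events; when high doses of systemic corticosteroid" are given, among other reasons. Their later imaging is lost. This does not reliably shrink the distortion: in the second model (median 52 weeks, half silent), letting 30% leave just after the irAE scan moved the ratio from 1.06 to 1.10.

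Fourth, handling of unscheduled scans often belongs in an analysis plan that is not shown. That is fair for the detail. It does not cover the contradiction over imaging, or the reason for each scan, which must be collected as the study runs.

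A reader might infer that irAE patients will come out worse in the reported analysis. The documents do not support that. The only survival comparison they name is a log-rank test, and on simple yes/no groups immortal time would push the result strongly the other way.

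**Conclusion.** The point holds in a limited form. Section 2.5.3 and Table 1 disagree on whether an irAE prompts imaging. If it does, the exploratory irAE comparison has unequal imaging, chiefly between week 28 and one year. With irAE treated as time-dependent and no true association, that alone gives a false rate ratio of about 1.02–1.13 over the year, for an assumed silent phase of 1 to 6 months. The larger late-window ratio of about 1.4 needs the 6-month assumption and should not be read as the effect on the comparison.

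Two stronger readings are tempting. One is that nobody is imaged after week 28 without an irAE: the article shows only that no study scan is scheduled, suspected progression still prompts one, and its list of triggers is open-ended. The other is that the primary biomarker results are distorted: no biomarker is a scan trigger, and the objective concerned is exploratory. Severity: minor.

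**What to change.** Reconcile section 2.5.3 with Table 1 on imaging at an irAE. Then, for this exploratory comparison only:

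- Record the reason or reasons for every unscheduled scan. A scan with any other trigger, such as suspected progression or deterioration, does not count as done solely for an irAE.
- Take response from the scheduled week-12 and week-28 scans.
- Treat irAE as a time-dependent variable.
- Date a progression first seen on an irAE-only scan before week 28 at the next scheduled scan, using its planned date if the patient has left the study.
- Report the comparison up to the week-28 scan alongside one-year PFS, and label the one-year result as subject to unequal imaging after week 28. Re-dating cannot extend past week 28, because no later scheduled scan exists.

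In simulation, re-dating and closing at the week-28 scan bring the false ratio back to about 1.00. Treating irAE as time-dependent deals with the larger immortal-time bias.

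The cost is a few sentences in section 2.5.4 and one data field, which has to be filled in while recruitment runs (to October 2025). No scan is added. The downside is small: responses seen only on irAE-prompted scans do not count, and the comparison with equal imaging does not use weeks 28–52.
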